## Abstract

**Background:**

Traditional randomized controlled trials are considered the gold standard for evaluating the efficacy of a treatment. However, in adherence research, limitations to this study design exist, especially when evaluating real-world applicability of an intervention. Although adherence interventions by community pharmacists have been tested, problems with internal and external validity have limited the usefulness of these studies, and further well-designed and well-conducted research is needed. We aimed to determine the real-world effectiveness of a community pharmacy adherence intervention using a robust study design. This novel design integrates cluster randomization and an outcome evaluation of medication adherence using a population-based administrative data source in the province of Saskatchewan, Canada.

**Methods/Design:**

Community pharmacies from across the province of Saskatchewan, Canada were randomized to deliver an adherence intervention to their patients or usual care. Intervention pharmacies were trained to employ a practical adherence strategy targeted at new users of statin medications. While randomization and implementation of the intervention occurred at the community pharmacy level, the outcome analysis will occur at the level of the individual subjects. The primary outcome is the mean statin adherence among all eligible new users of statin medications. Secondary outcomes include the proportion of new statin users who exhibit adherence ≥80%, and persistence with statin use.

**Discussion:**

This novel study design was developed to combine the rigor of a randomized trial with a pragmatic approach to implementing and capturing the results in a real-world fashion. We believe this approach can serve as an example for future study designs evaluating practice-based adherence interventions.

**Trial Registration:**

ClinicalTrials.gov no. NCT00971412.

## Introduction

Randomized controlled trials (RCT) are considered the gold standard design for the evaluation of treatment efficacy [1], and are increasingly being used for evaluating interventions aimed at improving medication adherence [2]. However, in adherence research, limitations to this study design exist. First, traditional RCTs require that all study participants are informed and consenting volunteers. This requirement likely pre-selects individuals who are at a lower risk for non-adherence, particularly for RCTs of behavioural interventions. Indeed, patients enrolling in clinical trials may be systematically different than those declining to participate[2,3]. In addition, when traditional RCT designs are used, the same health care professional is often forced to provide the adherence intervention and 'usual care' concurrently [4,5]. Clearly, contamination is unavoidable when the same health practitioner is providing the control and experimental conditions simultaneously [3].

Because of their accessibility and frequent interactions with patients, community pharmacists are considered ideally situated to deliver interventions aimed at improving medication adherence [3]. However, adherence interventions by community pharmacists have not consistently shown benefits [3,6]. One of the reasons may be that these studies are often plagued with methodological problems. Many studies do not report a power calculation, do not utilize proper randomization techniques or allocation concealment, and most do not provide adequate details of the intervention when reporting the results [7]. Furthermore, generalizability of successful interventions is often low because most health care professionals do not have the time or resources to implement complex study protocols [8-11]. As a result, little is known about the extent to which community pharmacists can influence adherence in real world settings.

We describe the design of a study aimed at evaluating the real-world effectiveness of an adherence intervention provided by community pharmacies; the Community Pharmacy Assisting in Total Cardiovascular Health (CPATCH) study. This prospective study employs a novel design that integrates cluster randomization with an evaluation of *all *at-risk patients using an administrative database. This design presented herein was developed to strengthen the external validity of research studies that examine adherence interventions while maintaining the high standards required for prospective clinical trials. Although the general CPATCH strategy is intended to be employable with all cardiovascular medications, this study is focused on the prevention of non-adherence among new users of statin medications. Statin medications were chosen for this initial study, as it is well known that 40% to 50% of all new statin users become non-adherent within the first year [12,13], and a sizeable proportion discontinue the medication after only one dispensation [14].

## Methods

### Recruitment of Community Pharmacies

In the Fall 2009, all community pharmacies across the province of Saskatchewan (n = 357) were invited to enrol in the CPATCH study. Advertisements were placed in bulletins and newsletters distributed by provincial pharmacy organizations. Also, individual letters were mailed to all pharmacy owners/managers in the province and the study investigators advertised in person at various local pharmacy conferences and events.

Community pharmacies interested in enrolling were directed to the study coordinating centre at the University of Saskatchewan to determine their eligibility. Pharmacies were eligible for enrollment if: i) they filled at least 85 total statin prescriptions during a consecutive 6 week period; ii) the owner/manager indicated that this adherence intervention would be given priority over all other study initiatives offered by the pharmacy staff; and iii) all members of the pharmacy (dispensary) staff provided informed consent.

### Randomization

The CPATCH study employed a clustered randomized trial design whereby community (retail) pharmacies were randomized into one of two groups: an intervention group that received training to provide the CPATCH adherence strategy to their patients; and a usual care group that did not receive any specialized adherence training and will provide their patients with standard care.

A computer generated randomization list, in permuted blocks of 6, was created by an employee at the Drug Information centre at the University of Saskatchewan who is not an investigator in this study. Each randomly allocated group assignment (intervention or usual care) was individually sealed in sequential, opaque envelopes and kept in the office of the Drug Information Centre. Given the nature of the intervention, it was impossible for the study investigators and pharmacy researchers (i.e. participating pharmacies) to be blinded to the group assignments; however, all study researchers were blinded to the sequence generation, and all allocations were concealed until the study group was assigned. Furthermore, randomization was carried out in multiples of 6 (i.e., six pharmacies were randomized at a time) to ensure that the investigators had no opportunity to anticipate which group a pharmacy would be allocated to.

### The Intervention

Pharmacies (i.e. pharmacists and pharmacy technicians) randomized to the intervention group received training on how to implement the CPATCH support program within their store; the control pharmacies did not receive any training, and were intentionally not given any indication of the focus of the study intervention (adherence of new statin users). Training on the CPATCH strategy was provided through a 2.5 hour workshop delivered in a setting outside the dispensary. Briefly, the training program introduced a simple and coordinated strategy to consistently identify and support patients at high risk for statin non-adherence. The criteria used to identify individuals at high-risk for non-adherence were based on epidemiologic observations of statin use. Specifically, individuals receiving their first dispensation for a statin medication have a 40%-50% of becoming non-adherent in the first year of therapy [12,13]. Further, many patients will discontinue after only one dispensation [14]. These dispensation patterns were used to provide objective evidence about the risk for non-adherence associated with new prescriptions for these medications. Also, these data were used to justify our hypothesis that initial statin dispensation encounters are critical to the prevention of non-adherence.

The CPATCH strategy was designed specifically to be implemented into real-world community pharmacy practice without the need for additional resources or significant changes to existing workflow procedures. As a result, the program is flexible to each specific pharmacy. The consistent elements of the overall CPATCH training strategy are: i) routine identification of new users (those in their first year of therapy) of statin medications as they present for each dispensation; ii) consistent assessment for barriers to non-adherence at every dispensation for at-risk patients (new users); iii) a paradigm shift from traditional counselling to an approach that focuses on patient preparation and reassurance; preparation for the negative messages about statins they will likely hear in the coming months and reassurance that this medication is backed by objective evidence, and iv) a commitment by pharmacy staff to actively respond to identified adherence barriers such as cost, intolerance, lack of knowledge, or beliefs about the medication. The focus of this strategy is to lower the incidence of non-adherence rather than remedy those patients with established non-adherence.

### Subjects

Intervention pharmacies will identify patients within the first year of statin therapy through dispensation records and face-to-face encounters. Although intervention pharmacies will target all statin users within their first year of therapy, data will only be collected on those subjects who: i) receive a new statin prescription from a study pharmacy (intervention or control) during the observation period; ii) have no statin fills recorded during the year prior to the index prescription (first fill for a statin medication during the study observation period); and iii) have been continuously enrolled as a Saskatchewan Drug Plan beneficiary for at least 365 days prior to the index prescription. These study subjects will be identified independently by personnel from the Saskatchewan Ministry of Health and all outcome data will be collected at the administrative database level (see "Follow-up").

The observation period for each pharmacy will begin two weeks after their training session. This two week lag period will be used to allow each staff to implement the strategy and resolve any issues with the help of the CPATCH investigators. To ensure consistency between groups, usual care pharmacies were assigned a start date that matched the date of an intervention pharmacy falling most closely in the order of randomization. As a result, in each permuted block of six randomized pharmacies, three pairs (one control and one intervention) of stores will share the same start date.

### Follow-up

All patient information and outcome data will be collected from administrative databases maintained by the Saskatchewan Ministry of Health (Sask Heath). Sask Health maintains a registry and several databases containing health-services records such as prescription drug data, hospital services data, and physician services data (Table 1). Health services information captured by distinct databases can be linked at the patient level through a unique identification number for each individual. These databases have served as the basis for many observational studies because they capture data on the vast majority of Saskatchewan residents [15-18]. For this study, the databases will be used to capture health services utilization (prescriptions, physician visits and hospitalizations) including diagnoses on all eligible subjects.

**Table 1 T1:** Relevant Data Elements Available from Saskatchewan Health Databases [18]

Database	Available Data
Prescription Drug	Patient information
	Drug information
	Prescriber information
	Dispensing pharmacy information
	Cost information

Hospital Services	Patient information
	Diagnostic and procedure information (based on ICD-10-CA^a ^and CCI^b^)
	Admission and discharge dates
	Length of hospital stay

Physician Services	Patient information
	Physician information
	Diagnostic information (3 digit ICD-9^c ^code)
	Billing information

Insurance registry	Beneficiary information (effective date, end date, sex, age, residence)

a. International Statistical Classification of Disease and Related Health Problems, Tenth Revision, Canada [35]

b. Canadian Classification of Health Interventions [36]

c. International Classification of Disease, Ninth Revision

All Saskatchewan residents are eligible for provincial health insurance coverage, except inmates of federal penitentiaries and members of the Royal Canadian Mounted Police and Canadian Forces (less than 1% of the Saskatchewan population). All health insurance beneficiaries are eligible for Saskatchewan Drug Plan benefits except those who receive these benefits from another government agency, primarily registered Indians (about 9% of the population). Therefore about 10% of the Saskatchewan population is ineligible for the study because of no or incomplete capture of health services information.

The researchers will provide Sask Health with the list of participating pharmacies and their specific Saskatchewan Drug Plan identifiers (i.e., provider identifier), and enrolment dates. Sask Health personnel will extract all statin prescriptions dispensed from the participating pharmacies during the 18 months following the pharmacy's enrolment date. The individuals receiving these prescriptions will form the pool of potential new statin-users. The prescription histories of the potential pool members will be reviewed to determine which subjects are new statin-users. Hospital, physician and prescription information for eligible new statin-users will be compiled and de-identified prior to release to the researchers for analysis.

It is estimated that each pharmacy will need six months to accrue their sample size of new statin users, thereby allowing 12 months for follow up. However, because it will not be possible to determine when each pharmacy's sample size has been met, data will be collected on all new-users presenting to each pharmacy throughout the observation period. Subjects will be followed from one year prior to their index prescription until the end of the pharmacy's observation period, death, or loss of beneficiary status, whichever is sooner.

### Outcomes

Although community pharmacies are the unit of randomization, our primary outcome is the mean statin adherence among all eligible new users of statin medications who have been followed up for at least 6 months past their index prescription. This primary outcome will be measured at the individual level. All statin dispensations for each subject will be captured by the prescription drug plan database and mean adherence will be measured using the proportion of days covered (PDC) [19,20], adjusted for any days that a subject may be hospitalized during the observation period. The PDC is calculated by taking the sum of the days' supply for all statin prescription fills during the study period, divided by the number of days of observation. Study participants who have statin dispensations from non-study pharmacies will be captured and accounted for using methods previously published [21]. Secondary outcomes include the proportion of new statin users who exhibit adherence (PDC) ≥80%, and the persistence with statin use among patients with a minimum of 12 months of follow up. Persistence is defined as the number of days from the index prescription to the earliest occurrence of study end date or date of discontinuation (assumed when a refill is not obtained within 102 days of finishing the estimated supply) [22,23]. Only those subjects with a minimum of 6 months of follow-up will be included in the secondary analyses.

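### The primary outcome is named a proportion of days covered, but its stated formula is a possession-type ratio that can exceed 1 and credits supply never used inside the observation window

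*Protocol article*

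**What the plan says.** The abstract (Methods/Design) sets the endpoint: "The primary outcome is the mean statin adherence among all eligible new users of statin medications". The Outcomes section then says that "mean adherence will be measured using the proportion of days covered (PDC) [19,20], adjusted for any days that a subject may be hospitalized". The following sentence gives the computation. The numerator comes from "taking the sum of the days' supply for all statin prescription fills during the study period"; the denominator is the patient's observed time in days.

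The hospital-day adjustment is the only modification stated. The article gives no upper limit, no cut-off for supply that outlasts the window, and no rule for supply replaced by a different statin.

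The same measure feeds a secondary outcome, "the proportion of new statin users who exhibit adherence (PDC) ≥80" per cent.

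The length of the window varies. Outcomes admits patients "who have been followed up for at least 6 months past their index prescription". Follow-up takes dispensings "during the 18 months following the pharmacy's enrolment date" and follows each patient to the end of the pharmacy's period, death or loss of coverage. Statistical Methods speaks of adherence at one year.

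**The concern.** The name and the formula describe different quantities. A proportion of days covered asks, for each day in the window, whether the patient had drug on hand; each day counts once at most, so the result lies between 0 and 1. The stated formula adds up everything dispensed and divides by elapsed time, which is a possession-type ratio. It differs from the named measure in three ways:

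- it has no ceiling;
- a fill near the end of the window counts in full, although most of it is for days not observed;
- when one statin is replaced by another, the abandoned remainder and its replacement both count.

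At stake are the primary mean and the 80% responder outcome. In the mean, patients scoring above 1 offset patients with poor coverage. In the responder outcome, a patient with long uncovered periods can pass the threshold. Because follow-up differs between patients, the same refill behaviour can also score differently according to when the patient entered.

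**Working it through.** **Inputs.** The formula, the 6-month minimum and the 80% threshold come from Outcomes, the 18-month period from Follow-up, and the one-year time point from Statistical Methods. I take 6, 12 and 18 months as 183, 365 and 548 days. The article gives no fill lengths; 100 and 34 days are assumptions. It also gives no worked score, so there is no figure of the plan's own to reproduce for this point.

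**Two calculations.**
- Formula as written: total days' supply ÷ days in window.
- Days covered: distinct days in the window with supply on hand ÷ days in window.

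| Fill pattern | Window | As written | Days covered |
|---|---|---|---|
| 100-day fills on days 0, 100, 200, 300 | 365 | 400/365 = 1.10 | 365/365 = 1.00 |
| 34-day fills every 34 days (11 fills) | 365 | 374/365 = 1.02 | 1.00 |
| 34-day fills every 30 days (13 fills) | 365 | 442/365 = 1.21 | 1.00 |
| 100-day fills on days 0, 100, 355 | 365 | 300/365 = 0.82 | (100+100+10)/365 = 210/365 = 0.58 |
| 100-day fills on days 0, 170 | 183 | 200/183 = 1.09 | (100+13)/183 = 113/183 = 0.62 |
| 100-day fill on day 0, replaced by 100 days of another statin on day 30, then none | 183 | 200/183 = 1.09 | 130/183 = 0.71 |

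Rows 1 to 3 show the missing ceiling. Rows 4 and 5 show supply past the end of the window; both patients pass 80% as written and fail on days covered. Row 6 shows replaced supply: the 70 days left from the first fill are counted although superseded.

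**Largest overhang from one last fill** (dispensed on the last day, so all but one day lies outside the window):

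| Fill length | 183 days | 365 days | 548 days |
|---|---|---|---|
| 100 days | 99/183 = 0.54 | 99/365 = 0.27 | 99/548 = 0.18 |
| 34 days | 33/183 = 0.18 | 33/365 = 0.09 | 33/548 = 0.06 |

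The error therefore shrinks as the window lengthens and as fills get shorter.

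**Misclassification is not automatic.** With 100-day fills on days 0, 150, 250 and 350 over one year, the formula gives 400/365 = 1.10 and days covered are (100+100+100+15)/365 = 315/365 = 0.86. The score is too high, but both values are above 0.80.

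**The case against.** The strongest defence is that the article condenses a fuller protocol, cites sources for the PDC, and may simply have worded it loosely; ceiling, carry-forward and truncation rules are details that an article may leave to other documents. That is fair as far as omissions go. But the article does not leave the calculation open: it states a formula, and the formula is not that of the measure it names. The citation on dispensings from non-study pharmacies is not offered as a correction to it.

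It is also fair that the size depends on unstated fill lengths and that one-year windows give smaller errors than six-month ones. Reclassification at one year takes a pattern such as a long gap followed by a late fill. Part of a proper definition is already present: fills of any statin count, and hospital days are to be adjusted for.

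Four stronger readings are tempting and are not supported:

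- *All overlapping supply is wrongly credited.* Early-refill supply that is used later inside the window is legitimate coverage once it is carried forward. Two 100-day fills of the same drug on days 0 and 30 cover all 183 days. The errors are the missing ceiling, the overhang and the replaced supply.
- *Follow-up length differs by arm, so the error must too.* Subjects gives paired intervention and control pharmacies the same start date, and Follow-up applies one 18-month extraction to all. Follow-up is largely balanced by design.
- *A patient-level error of about 0.10 is as large as the planned effect.* The planned effect is a difference between arm means, and an error common to both arms largely cancels in it. The value 0.71 × 0.15 = 0.1065 also reads the 15% in Sample Size as relative, which the article does not say.
- *The intervention acts on supply, so it must inflate the ratio.* The Intervention lists cost, intolerance, lack of knowledge and beliefs as barriers; supply is not among them.

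**Conclusion.** The point holds as a wrongly stated rule for the primary outcome and for the 80% secondary outcome. The measure as defined is not a proportion of days covered: it can exceed 1, and it credits in full supply beyond the window and supply replaced after a switch. Assuming 100-day fills, continuous supply scores 1.10 at one year, and a patient with 0.58 of days covered can score 0.82 and be classed as adherent. A single last fill can add up to 0.54 at 6 months and 0.18 at 18 months; with 34-day fills these fall to 0.18 and 0.06.

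These are errors in individual scores. No between-arm bias has been calculated, and the article gives no data from which to calculate one. Bias is possible, for example if responses to intolerance change how often statins are switched, or responses to cost change fill size, in one arm only. It is not certain.

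**What to change.** Replace the formula in Outcomes with a count of covered days:

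- Numerator: distinct days in the patient's observation window with any statin supply on hand.
- Carry early-refill supply forward.
- Do not count replaced supply a second time after a switch.
- Cut supply off at the end of the window.
- Remove inpatient days from numerator and denominator.
- The maximum is then 1.

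Use this measure for both the primary mean and the 80% outcome, and keep the current ratio, under its own name, as a sensitivity analysis.

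The cost is a reworded definition and a changed derivation programme on the same dispensing and hospital records. No new data are needed.

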***Pharmacy Level***		

Pharmacy Type	Indicates the type of pharmacy (mass merchandise, chain/grocery, independent) [38]	Investigators to categorize

Pharmacy Location	Rural (population < 10,000)	Investigators to categorize
	Regional (population 10,000 - 100,000)	
	Urban (population > 100,000)	

Prescription Volume	Mean number of new statin prescriptions filled monthly (proxy measure for prescription volume)	Prescription Drug

Pharmacist Coverage	Pharmacist overlap or single pharmacist	Pharmacy survey

Technician Support	Pharmacy technician support	Pharmacy survey

Two secondary endpoints, the proportion of new statin users who exhibit optimal adherence (≥80%) at one-year and mean persistence will be measured on an individual level and analyzed using GEE with an exchangeable correlation matrix and robust standard errors. All analyses will be intention-to-treat, and will include any pharmacies that have withdrawn, as well as any individual subjects who are no longer beneficiaries of the Saskatchewan Drug Plan (due to death or coverage termination). Mean imputation will be used for subjects or pharmacies lost-to-follow-up.

Ethics approval for the study protocol was obtained from the University of Saskatchewan Biomedical Ethics Board (09-135). The study is registered at ClinicalTrials.gov no. NCT00971412.

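### Persistence is a censored time analysed as a plain mean, so its level and the size of the arm difference depend on accrual and on the minimum follow-up applied, although the between-arm test stays roughly valid

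*Protocol article*

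**What the plan says.** Outcomes gives the definition: "Persistence is defined as the number of days from the index prescription to the earliest occurrence of study end date or date of discontinuation". Discontinuation is "assumed when a refill is not obtained within 102 days of finishing the estimated supply". The outcome is introduced as "persistence with statin use among patients with a minimum of 12 months of follow up", and the same paragraph closes with "Only those subjects with a minimum of 6 months of follow-up will be included in the secondary analyses".

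Statistical Methods, in the text after Table 2, gives the analysis: "mean persistence will be measured on an individual level and analyzed using GEE with an exchangeable correlation matrix and robust standard errors". No event indicator, common horizon or time-to-event method is attached to it. The same paragraph says that the intention-to-treat analyses "will include any pharmacies that have withdrawn, as well as any individual subjects who are no longer beneficiaries of the Saskatchewan Drug Plan", and that "Mean imputation will be used for subjects or pharmacies lost-to-follow-up".

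Three further facts matter:

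- Follow-up: prescriptions are extracted for 18 months per pharmacy, and new users are taken in for the whole of that time.
- Follow-up: a subject's observation ends with the window, at death or on loss of coverage. The planning assumption is six months of accrual, leaving twelve months of follow-up.
- Subjects: within each block of six, control and intervention stores are paired on start date.

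**The concern.** The defined quantity mixes two kinds of number. For a patient who stops, it is a time on treatment. For a patient who does not, it is the length of follow-up, which is fixed by the index date and says only that time on treatment is at least that long. Averaging the two as complete observations gives a mean that reflects the accrual calendar as well as behaviour. A reader would naturally take it as average time on statins or as one-year persistence, and compare it with other studies. It is neither.

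Two details add to this. A stop can be confirmed only after 102 days without a refill, so stopping late in follow-up may go unrecorded. And the text gives two minimum follow-up periods that could apply to persistence, each of which leads to a different mean.

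**Working it through.** The protocol gives no mean, SD, hazard or power for persistence, so it has no figure of its own to reproduce. Its timeline does reproduce: 18 − 6 = 12 months.

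**1. Range of scores for a patient who never stops.** The window is 18 months, about 547.5 days. With a 12-month minimum, follow-up and hence the score runs from 365 to about 547 days. With a 6-month minimum it runs from about 182 to 547 days.

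**2. The 102-day gap, if discontinuation is dated at the end of supply.** The last confirmable stop is follow-up minus 102:

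| Follow-up (days) | Last confirmable stop | Share of follow-up that is blind |
|---|---|---|
| 182.5 | 80.5 | 102/182.5 = 56% |
| 365 | 263 | 102/365 = 28% |
| 547.5 | 445.5 | 102/547.5 = 19% |

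Knowing a subject's status at day 365 takes 365 + 102 = 467 days of follow-up, so an index date in the first 547.5 − 467 = 80.5 days of the window.

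**3. Effect on the mean (simulation, 2,000,000 subjects per setting).** These inputs are assumptions: uniform entry; 40%, 45% or 50% stopped by 12 months; 15% stopping after the first fill; 34- or 90-day fills; stops at the end of supply; and, for an arm effect, a hazard ratio of 0.75. The 40–50% range is borrowed from the Introduction, where it describes one-year non-adherence, not stopping.

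| Quantity | 12-month minimum | 6-month minimum |
|---|---|---|
| Values that are just length of follow-up (45%, 34-day fills) | 57% | 65% |
| Same, over all assumptions | 52–65% | 61–73% |
| Mean persistence (45%, 34-day fills) | 318 days | 267 days |
| Arm difference at hazard ratio 0.75 (45%, 34-day fills) | 28.9 days | 21.0 days |

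The gap in the mean for identical behaviour is 51 days (46 to 58 over all assumptions). A hand check agrees: mean follow-up is (365 + 547.5)/2 = 456 against (182.5 + 547.5)/2 = 365 days, a difference of 91, and 51/91 = 0.56, close to the share of values that are simply follow-up.

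**4. Comparison between arms.** With equal follow-up and no effect, a t-test on cluster means (15 v 15 pharmacies of 25, 4000 runs, standing in for the GEE) rejected in 5.4% of runs against a nominal 5%. If one arm's mean follow-up is longer by 7, 14 or 30 days, a false difference of 3.4, 7.0 or 14.9 days appears; about half of any imbalance passes through.

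**5. Effect of the 102-day gap.** Over all assumptions it raises the mean by 3.2 to 6.3 days and shrinks the arm difference by 0.4 to 1.1 days. It matters more for proportions: 14–19% of true stoppers (12-month minimum) or 18–28% (6-month minimum) are recorded as persistent to the end.

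**6. Check of the remedy (45%, 34-day fills).** Subjects not known to have stopped are censored at end of follow-up minus 102 days, and the horizon is 365 days.

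| | 12-month minimum | 6-month minimum |
|---|---|---|
| 12-month persistence, estimate (truth) | 56.9% (56.9%) | 57.0% (57.0%) |
| Restricted mean in days, estimate (truth) | 267.3 (267.3) | 267.7 (267.6) |
| 12-month persistence if censored at end of follow-up instead | 58.7% | 63.6% |

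The two minimums now agree. The uncorrected 6-month mean of 267 days in step 3 lies near this restricted mean only by coincidence: mean follow-up there happens to be 365 days.

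**The case against.** A reader might infer that the persistence result is unusable or that the arm comparison is biased. The documents do not support that. Every pharmacy has the same 18-month window and start dates are paired across arms, so follow-up should be similar in both. The GEE then estimates a difference in restricted means averaged over the realised follow-up, with about the nominal error rate. This stands. What remains against the plan is the interpretation of the level, the size of the difference, and exposure to chance imbalance in follow-up.

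A reader might also infer that the 102-day gap seriously distorts the endpoint. At exactly the minimum follow-up, the share of stoppers missed looks large: 19% at 365 days and 39% at 182 days in an illustration with 12% stopping at day 34 and 45% by one year. But those figures do not describe the average subject, and the planned endpoint is mean days, which hardly moves. The blind period also presumes that discontinuation is dated at the end of supply, and the article does not say so. If it is dated 102 days later, a subject inside the gap has not yet discontinued and is not misclassified.

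Nor do the two minimums strictly contradict each other. Six months can be a floor for all secondary analyses and twelve a stricter rule for persistence, which is the more natural reading. The text does not say so, and neither minimum is squared with the statement that subjects who died or lost coverage are included.

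Lastly, if study end meant day 365 for each subject with at least 12 months of follow-up, the mean would be a proper one-year restricted mean apart from the 102-day issue. Nothing in the text says this; the one-year wording in Statistical Methods attaches to adherence. The condensed article is no answer either, because it states both the definition and the method, and the two do not fit.

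**Conclusion.** The point holds in a limited form. Mean persistence as planned is not time on treatment and not one-year persistence. More than half of its values would be lengths of follow-up under every assumption tried. The choice of minimum alone would move the mean by about 50 days, and the arm difference from 28.9 to 21.0 days in the illustration. These sizes rest on assumed stopping rates, fill lengths and uniform entry; the 365-to-547-day spread for a patient who never stops follows from the protocol's dates alone.

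The test between arms remains roughly valid while follow-up is balanced. The 102-day gap is a minor matter for the mean and a real one for any proportion persistent. The 12- and 6-month sentences need reconciling but are not a contradiction. This is a secondary outcome, and correcting it before analysis is worthwhile because the correction is cheap.

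**What to change.** Analyse persistence as a censored time to discontinuation with a common 365-day horizon. A restricted mean or Kaplan-Meier persistence at 365 days fits the stated interest in mean persistence; a marginal Cox model is an alternative. Any of them needs pharmacy-clustered variance.

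State that discontinuation is dated at the end of the estimated supply. Censor each subject not known to have stopped at the end of follow-up minus 102 days. If the date is instead set 102 days later, this censoring rule has to be revisited.

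Replace the 12- and 6-month sentences by one rule for persistence, and make it consistent with the inclusion of subjects who died or lost coverage. Once censoring is handled, either minimum targets the same quantity. Dropping the minimum altogether gains less than it seems, because subjects with 102 days of follow-up or less contribute no information.

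Cost: revised wording and standard software, on data already being collected. The downside is that each subject's last 102 days serve only to confirm status. As a result, day 365 itself is informed only by subjects with at least 467 days of follow-up: under uniform entry, 80.5/182.5 = 44% of those with a 12-month minimum, or 80.5/365 = 22% with a 6-month one. Later entrants contribute to the earlier part of the curve.
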